#### Neuromuscular outcome (FRP)

The root mean square (RMS) of the EMG signals will be calculated using a sliding window of 1 s with a step size of 50 ms.^50^

The three phases of the flexion-extension cycle—flexion, relaxation and extension—will be manually identified on the RMS signal, and the peak value for each phase will be recorded.

The flexion–relaxation ratio (FRR) will be computed by dividing the peak EMG activity during the flexion phase by that of the relaxation phase. Preintervention and postintervention FRR values will be compared using a paired t-test to assess statistical significance. If the assumption of normality is not met, the non-parametric Wilcoxon signed-rank test will be applied instead.

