#### Neuromuscular outcome

The FRP corresponds to a myoelectric silence of erector spinae during maximal forward bending. The FRP is reduced or abolished in approximately half of individuals with LBP.^44^

It will be assessed at baseline and post-intervention (week 4) to evaluate potential restoration. A sEMG system (model Trigno, Delsys, Boston, Massachusetts, USA) will be used with a sampling frequency of 1000 Hz. The skin at the electrode sites will be shaved, abraded and cleaned with alcohol, prior to data collection. Electrodes will be placed over the left and right longissimus dorsi (at the level of the L1 spinous process) and the left and right multifidus muscles (at the L5 level) aligned with the orientation of the muscle fibres and according to the recommendations of the Surface Electromyography for Non-Invasive Assessment of Muscles projects.^45^ Standardised instructions will be provided to all participants to ensure consistency in movement execution. Participants will be instructed to stand upright with their arms relaxed at their sides, eyes directed forward and level. They will then be asked to bend forward into maximal trunk flexion while maintaining their knees fully extended, allowing the upper body and arms to hang freely in a relaxed manner.

The movement sequence will be divided into four distinct phases, each lasting five seconds^46^: (1) static upright standing, (2) forward bending into full flexion, (3) static maintenance of full flexion and (4) return to the initial upright standing posture. Specifically, participants will first maintain a neutral standing position for 5 s, followed by a controlled descent into maximal forward flexion over 5 s. They will then hold the fully flexed position statically for an additional 5 s before returning to the starting posture over the final 5 s.

To ensure correct execution, an experimenter will demonstrate the movement sequence and pacing prior to the trials. A metronome will be used to regulate timing and promote temporal consistency across participants. Each participant will perform three consecutive trials per set, and the entire sequence will be repeated twice.

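### Scoring the relaxation phase by the peak of a 1-s sliding RMS between hand-marked borders makes the flexion–relaxation ratio depend on border placement and can compress it in muscles that do relax

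*Protocol article*

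**What the plan says.** Under Outcomes, Neuromuscular outcome, the protocol article defines the phenomenon as a low-level state: "The FRP corresponds to a myoelectric silence of erector spinae during maximal forward bending". On timing it says "The movement sequence will be divided into four distinct phases, each lasting five seconds": standing, bending, static full flexion, return. On the third phase: "They will then hold the fully flexed position statically for an additional 5 s". A metronome paces the movement. EMG is recorded at a "sampling frequency of 1000 Hz".

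Under Statistical analysis, Neuromuscular outcome (FRP), the RMS is "calculated using a sliding window of 1 s with a step size of 50 ms". The flexion, relaxation and extension phases "will be manually identified on the RMS signal, and the peak value for each phase will be recorded". The FRR is obtained by "dividing the peak EMG activity during the flexion phase by that of the relaxation phase". FRR values before and after the intervention are then compared with a paired t-test, or a signed-rank test if normality fails.

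The article therefore fixes three things together: a 1-s window, borders placed by hand on the smoothed trace, and the maximum as the summary of the relaxation phase.

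**The concern.** Silence is a property of the lowest part of the trace, yet it is summarised by the highest value in the phase. The hold has movement on both sides. A centred 1-s window whose midpoint is less than 0.5 s inside the hold already contains bending or rising activity; a leading or trailing window would reach up to 1 s past one border. Taking the maximum means that one such window sets the denominator, however quiet the others are. The borders are drawn on a trace in which the edge of silence has already been blurred by the same window.

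Restoration of flexion–relaxation at week 4 is a named secondary objective. Compression acts mainly on muscles that do fall silent, which are the ones that would show restoration. Variation in border placement adds noise to a before–after comparison in at most 48 people.

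**Working it through.** **The plan's own figure.** The article states no FRR value, so there is none to reproduce. Its only design figure, 22 per group for COMI (difference 2.6, SD 3, two-sided 0.05, 80% power), reproduces: exact t-test power is 0.802 at 22 and 0.782 at 21. This point does not depend on it.

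**Inputs from the article.** 5-s phases, 1-s window, 50-ms step, 1000 Hz sampling, peak per phase, FRR = peak flexion / peak relaxation.

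**Assumptions.** EMG amplitudes, and how movement activity starts and stops at the edge of the hold. The article gives neither.

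**Step 1: one mixed window, abrupt edge.** Let a share q of the 1-s window overlap movement at amplitude F, with the rest silent at S. Then RMS = √(qF² + (1−q)S²) and FRR = F/RMS. With F = 40 µV and S = 5 µV, the true FRR is 8.0. At q = 0.10: √(0.10×1600 + 0.90×25) = √182.5 = 13.5 µV, so FRR = 40/13.5 = 3.0.

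**Step 2: the same case with tapered activity.** Let the movement activity rise from zero at the border and add its power to the silent level, so that RMS² = S² + ∫A(t)²dt over the overlap of u seconds. For a linear ramp reaching F in 1 s, the integral is F²u³/3. At u = 0.10 it is 1600×0.001/3 = 0.53, so RMS = √25.53 = 5.05 and FRR = 7.9. For a half-sine over 5 s, A(t) = F·sin(πt/5).

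| Overlap of the window | Abrupt | Linear ramp, 1 s | Half-sine, 5 s |
|---|---|---|---|
| 5% | 3.9 | 7.99 | 8.0 |
| 10% | 3.0 | 7.9 | 7.97 |
| 25% | 2.0 | 6.9 | 7.5 |
| 50% | 1.4 | 4.2 | 5.6 |

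The shape of the activity at the border matters more than the amplitudes. With F = 60 and S = 5 (true FRR 12.0), the abrupt figures are 4.2, 3.1, 2.0 and 1.4.

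**Step 3: simulation of the stated scoring.** 1000 Hz, 5-s phases, centred 1-s RMS, 50-ms step. Assumed amplitudes: flexion 50, extension 100, silent level 2.5 (true FRR 20). Bursts meet the hold edges directly.

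| Border inside the hold by | Peak rule, abrupt | Peak rule, half-sine |
|---|---|---|
| 0 s | 0.73 | 3.8 |
| 0.25 s | 1.05 | 10.0 |
| 0.4 s | 1.63 | 18.8 |
| 0.5 s | 20.0 | 19.1 |

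If the muscle falls silent 1 s before the hold and rising activity starts 0.5 s after its end, the peak rule gives 19.9 (abrupt) or 19.0 (half-sine) even with borders at the hold edges.

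**Step 4: restoration from a true FRR of 2 to 20, borders at the hold edges.** Recorded as 0.71 to 0.73 with abrupt bursts, and as 1.9 to 3.9 with half-sine bursts. With borders 0.5 s or more inside, it is recorded as about 2 to 20 (abrupt) or 1.9 to 19 (half-sine).

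**Step 5: the alternative.** Mean RMS over the middle 3 s of the hold gives 20.7 (abrupt) and 19.9 (half-sine). Even with borders wrongly left at the hold edges, the mean gives 5.5 and 16.4, against 0.73 and 3.8 for the peak.

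**The case against.** Four arguments weigh against the point.

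First, the large losses need an abrupt edge. The article describes a controlled 5-s descent and a 5-s return, so tapered activity is at least as plausible, and a 100-ms overlap then costs about 1% or less. A reader might infer that a 100-ms border shift more than halves the ratio; that holds only for the abrupt case.

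Second, a rater who sees the smoothed flanks can leave them outside the trough. A 5-s hold leaves about 4 s of clean windows, and borders 0.5 s inside remove the spill. Nothing says the borders are put at the hold edges.

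Third, a border rule may stand in the full protocol or in the cited sources, which are not shown. The absence of such a rule from a condensed article is not itself an error.

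Fourth, the article gives no FRR cut-off, so the stronger reading that a silent muscle would be classed as impaired has no threshold behind it. It also specifies no FRR correlation analysis; only the general hypothesis that neurophysiological changes track clinical improvement could cover one.

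All four stand as limits on size. They do not remove the point, which concerns what the article does state: a maximum over a phase flanked by movement, taken from a 1-s smoothed trace. Its result is sound only if every border is placed well inside the hold, and the stated rule does not secure that. On repeats the article says "Each participant will perform three consecutive trials per set, and the entire sequence will be repeated twice". Averaging repeats, if done, would reduce random placement error but not the upward pull of a maximum.

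**Conclusion.** The concern holds in a limited form. The stated scoring can compress the FRR of a muscle that relaxes and makes it depend on border placement. The loss runs from negligible (tapered activity with a small overlap, or borders at least 0.5 s inside the hold) to large (abrupt activity with borders at the hold edges: a true 20 scored as 0.73). The direction follows from the window and the maximum; the size rests on assumed amplitudes and burst shapes.

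Two stronger readings are not supported. A reader might infer that restoration would be hidden: this happens only with abrupt activity and borders at the hold edges, while with half-sine activity it is strongly shrunk but still visible. A reader might also infer bias between arms: assessors and analysts are blinded to allocation, so the expected effect is attenuation and noise. Secondary outcomes are declared exploratory, and the COMI analysis, the sample size and the main conclusion are unaffected. It is worth correcting before FRR values are analysed, as a modest improvement.

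**What to change.** Under Statistical analysis, Neuromuscular outcome (FRP), replace the peak of the relaxation phase with the following rule: *relaxation is scored as the mean RMS over the central part (about 3 s) of the identified 5-s static hold, using only windows that lie wholly inside the hold (centres at least 0.5 s from each border), with the same rule at both visits.* Keep the peak for the flexion phase.

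Locate the hold by metronome timing if the metronome is synchronised with the EMG record, which the article does not say; otherwise locate it from the trace. A central 3 s leaves 1 s at each end, so centred windows keep 0.5 s of slack for participants who move slightly off the beat.

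Report the peak-based FRR as a sensitivity version. Keeping the peak but restricting it to windows wholly inside the hold also recovers about 19 to 20 in the simulation, so the guard interval does most of the work; the mean adds protection when a border is misplaced.

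The cost is one sentence and a change to the scoring, applied to signals already recorded. The downside is slightly less comparability with peak-based FRR values: in a clean hold the mean lies a little below the peak, which raised the simulated FRR by about 3% (20.74/20.06 = 1.03).

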### Objectives and hypothesis

The primary objective of this study is to compare the effectiveness of repeated nine sessions of anodal tDCS targeting the DLPFC combined with an intensive exercise programme to nine sessions of sham tDCS combined with the same exercise programme. The comparison will focus on pain intensity and the multidimensional impact of pain in patients with CLBP immediately after the intervention.

The secondary objectives are to assess the effects of repeated sessions of tDCS over the DLPFC combined with an exercise programme on:

Pain, disability and psychological factors:Pain intensity, multidimensional impact of pain, functional disability and psychological outcomes (including fear-avoidance beliefs, catastrophising, anxiety and depression) immediately after the intervention (week 4), with follow-ups at 12 and 24 weeks.Functional brain connectivity:Changes in functional resting-state brain connectivity as evaluated by electroencephalography (EEG) over the DLPFC and its associated neural networks, between baseline and immediately after the intervention (week 4).Neuromuscular function of the erector spinae:The restoration of the flexion–relaxation phenomenon (FRP) in the erector spinae during forward bending was assessed immediately after the intervention (week 4).

We hypothesise that anodal tDCS targeting the DLPFC, combined with an intensive exercise programme, will lead to greater improvements in all clinically measured outcomes compared with sham tDCS combined with the same exercise programme, both immediately after the intervention (week 4) and at the 12- and 24-week follow-ups. Regarding functional brain connectivity, we hypothesise an increase in DLPFC connectivity with associated areas, and for the neuromuscular function, a restoration of FRP in the erector spinae muscles. Further, the magnitude of these neurophysiological changes will correlate with clinical improvements.

This protocol is version 1.0, dated 12 February 2026.

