### Randomisation/blinding

A randomisation list (using permuted blocks of randomly varying sizes 4, 6 or 8) will be generated by an independent research assistant using a computer-generated random number system (https://www.sealedenvelope.com/). To ensure allocation, consecutively numbered, sealed opaque envelopes will be used. Participants will be randomly assigned in a 1:1 ratio to receive either an anodal tDCS combined with an exercise programme or a sham tDCS combined with the same exercise programme. Patient-reported outcomes will be completed by participants themselves through an online procedure using Research Electronic Data Capture (REDCap), a secure, web-based platform designed to facilitate data collection in research studies.^38^ This system ensures that outcome assessors remain blinded, preventing any potential bias in data collection.

Neurophysiological and neuromuscular outcomes will be collected by trained assessors who are not involved in treatment delivery and who are blinded to group allocation.

The researchers responsible for data analysis will be blinded to treatment allocation. Similarly, all outcomes’ assessors and statisticians will remain blinded.

Both participants and the physiotherapist administering the exercise programme and the application of tDCS will also be blinded to treatment allocation. To ensure blinding, an independent research assistant will have previously programmed the *double-blind mode* available in the device’s software interface (DC-stimulator; Soterix Medical, New York, USA). This mode allows the system to automatically generate either an active or sham stimulation after the parameters for both options have been configured. The system can be operated in a special password-protected mode, ensuring that the information displayed on the screen does not reveal whether the stimulation is active or sham. The research assistant will assign a unique session-specific code to be provided to the physiotherapist before each session. Emergency unblinding will only be conducted in the event of a serious adverse event that is both unexpected and suspected to be related to the intervention.

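### The flexion–relaxation phases are marked by hand and tested before versus after, but the stated blinding covers treatment allocation only, not the visit

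*Protocol article*

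**What the plan says.** All references are to the Protocol article.

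- **Reading of the trace** (Statistical analysis, Neuromuscular outcome (FRP)): the RMS of the EMG signal is "calculated using a sliding window of 1 s with a step size of 50 ms". The flexion, relaxation and extension phases "will be manually identified on the RMS signal, and the peak value for each phase will be recorded". The FRR is obtained by "dividing the peak EMG activity during the flexion phase by that of the relaxation phase".
- **Test** (same section): "Preintervention and postintervention FRR values will be compared using a paired t-test to assess statistical significance", with the Wilcoxon signed-rank test if normality fails. No between-group test of FRR is stated, nor whether the paired test is run per arm or on both arms together.
- **Blinding** (Randomisation/blinding): neuromuscular outcomes are collected by assessors "who are not involved in treatment delivery and who are blinded to group allocation". Separately, "The researchers responsible for data analysis will be blinded to treatment allocation". Study design lists who is blinded and adds no factor other than allocation.
- **Expected direction** (Objectives and hypothesis): "for the neuromuscular function, a restoration of FRP in the erector spinae muscles". The Outcomes section adds: "It will be assessed at baseline and post-intervention (week 4) to evaluate potential restoration".

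**The concern.** Blinding protects a comparison only when it hides the factor being compared. For FRR the only stated comparison is between visits, while the stated blinding hides the arm. The phase borders that fix the ratio are set by judgement on each trace, with no algorithm or border rule given, and the hoped-for direction is declared in advance. If visit labels or recording order are visible during marking, a small habitual difference in where borders go on week 4 traces becomes a systematic change in FRR. The paired test would report that difference as restoration, or a difference in the other direction could hide a real change.

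**Working it through.** **1. The plan's own figure.** No sample size or effect is given for FRR. The stated 22 per group is for COMI (difference 2.6, SD 3, two-sided α 0.05, 80% power). It reproduces: the noncentral-t power is 0.782 at 21 and 0.802 at 22 per group. It is used below only to supply the number of pairs: 22 for one arm, 2 × 22 = 44 if the arms are pooled.

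**2. Is the ratio sensitive to border placement?** Assume a toy trace with amplitude 1 in flexion, 0.2 in the hold and 1.3 in extension, with abrupt edges. A centred 1 s RMS window near the end of the hold takes in a share w of the extension burst, so

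RMS = √(w × 1.3² + (1 − w) × 0.2²), and FRR = 1 / (peak RMS in the marked relaxation phase).

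The worst point is the last 50 ms step inside the marked border.

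| Border inside the hold | w | Peak RMS in relaxation | FRR |
|---|---|---|---|
| 0 s | 0.45 | √0.7825 = 0.885 | 1.13 |
| 0.25 s | 0.20 | √0.37 = 0.608 | 1.64 |
| 0.30 s | 0.15 | √0.2875 = 0.536 | 1.87 |
| 0.50 s or more | 0 | 0.20 | 5.0 |

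One extra RMS step inwards, from 0.25 to 0.30 s, raises FRR by 1.87/1.64 − 1, about 13%. Beyond 0.5 s, moving the border changes nothing. A second assumed envelope gave 3% to 22% for the same 0.05 s step with borders 0.25 s inside the hold, and nothing at 0.5 s or more. With gradual transitions the sensitive zone is wider: under another set of assumptions the effect disappears only from about 1 s. The sensitivity is real, but its size depends on features the article does not give.

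**3. Effect on the paired test.** Let b be the mean visit-dependent shift, in SDs of the paired difference, with no true change. The test statistic is noncentral t with n − 1 df and noncentrality b√n. The rejection rate is P(|T| > t at 0.975).

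| b (assumed) | 22 pairs (critical t 2.080): b√n | Rejects | 44 pairs (critical t 2.017): b√n | Rejects |
|---|---|---|---|---|
| 0 | 0 | 5% | 0 | 5% |
| 0.1 | 0.47 | 7% | 0.66 | 10% |
| 0.2 | 0.94 | 15% | 1.33 | 25% |
| 0.3 | 1.41 | 27% | 1.99 | 49% |
| 0.5 | 2.35 | 61% | 3.32 | 90% |

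The bias can also hide an effect. A true 0.6 SD change reduced by 0.3 SD falls from 77% to 27% power with 22 pairs, and from 97% to 49% with 44.

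**4. Linking steps 2 and 3.** If the SD of the change in log FRR is assumed to be 0.3 to 0.5, a shift of 0.2 to 0.3 SD is a change in FRR of exp(0.2 × 0.3) − 1 = 6% up to exp(0.3 × 0.5) − 1 = 16%. This falls within the 3% to 22% above. It shows that 0.2 to 0.3 SD is conceivable, not that it is expected.

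**5. Between-group comparison.** Simulated with the same shift in both arms (22 per arm, b up to 0.5), a two-sample t-test of change rejects in about 5% of trials. A visit bias common to both arms cancels.

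**The case against.** The strongest reply is that the point argues from silence. The article nowhere says that the marker sees the visit or the recording order, and how traces are coded for reading is often left to a full protocol or laboratory procedure. A reader might infer that the FRP reading is unmasked and its result therefore biased. The documents do not support that. What stands is narrower: the article says who is blinded and to what, and that factor is not the one its FRP test compares.

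Other replies and what remains of them:

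- **The sentence on neuromuscular assessors concerns those who collect recordings.** Correct. They meet the participant at baseline and week 4 and cannot sensibly be blinded to visit. Masking belongs to whoever marks the stored traces, who is closer to the analyst sentence.
- **The movement is paced by a metronome in 5 s phases, with demonstration and repeated trials.** This narrows the freedom to place borders. It does not remove it, because borders are set on the RMS trace and not at metronome times.
- **The magnitude rests on stacked assumptions.** Correct. Noise, amplitudes, transitions, usual border position, SD and the shift are all assumed, the shift must run the same way on average across participants, and the result includes nil.
- **The larger FRP issue is the missing comparison between arms.** That is a separate matter. Once FRR change is compared between arms, a common visit bias cancels, and only statements of restoration within an arm stay exposed.
- **The same argument might seem to cover visual rejection of EEG epochs.** It does not: the EEG outcome is tested between groups.

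**Conclusion.** The point holds as a mismatch between the stated blinding and the stated FRP test, conditional on the marker being able to tell the visit. No bias is shown and none can be sized from the article. The 15% to 27% (22 pairs) and 25% to 49% (44 pairs) rejection rates follow from an assumed 0.2 to 0.3 SD shift with no true change. With borders consistently well inside the hold, the shift could be zero and the test would keep its 5% level. The outcome is exploratory under Secondary analysis, and the self-completed COMI is not touched. Severity is minor. It is worth acting on because the safeguard is cheap and can still be applied to stored signals.

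**What to change.** In the statistical section on the neuromuscular outcome (FRP), state that:

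- EMG traces are exported under random codes that hide participant, group and visit;
- baseline and week 4 traces are marked in random order;
- the visit label is restored only after the FRR values are locked.

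The analyst sentence under Randomisation/blinding may be extended to say that the person marking the traces is blinded to visit as well as allocation. The sentence on the assessors who record the sEMG should stay as it is. No change to the EEG procedure follows from this point.

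If a between-group comparison of FRR change is added, masking remains useful for any statement of restoration within an arm.

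Cost: a file-renaming script, a short text change, and one re-marking of any traces already read. No new visit, procedure or staff.

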## Materials and methods

### Study design

This study is a triple-blind, parallel-group, randomised sham-controlled trial (RCT). The participants will be blinded to their treatment allocation. Blinding will be maintained for the physiotherapists, outcomes evaluators and statisticians.

The trial will consist of four assessment time points: baseline, 4 weeks (immediately postintervention), 12 weeks and 24 weeks of follow-up. The intervention will include nine treatment sessions over a 3-week period (figure 1).

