## Discussion

This randomised controlled trial is, to date, the first to investigate the effects of repeated sessions combining physical exercises with anodal tDCS targeting the PFC in individuals with CLBP. Previous studies involving tDCS in CLBP have primarily targeted the motor cortex.^20^ Exercise is currently the most widely recommended intervention for CLBP according to international clinical guidelines^52^ and its effects are thought to be partially explained by neurophysiological mechanisms.

While exercise-induced hypoalgesia is well-documented in healthy individuals, this mechanism appears to be attenuated or altered in patients with musculoskeletal pain conditions.^34 53^ We hypothesised that applying anodal tDCS over the PFC during exercise may enhance descending pain inhibition pathways and result in clinically meaningful improvements in both pain and disability among patients with CLBP.

In addition, the inclusion of neurophysiological (EEG) and neuromuscular (FRP) outcome measures may help elucidate the underlying mechanisms of action. This study has several strengths. First, it is designed to provide evidence regarding the efficacy of combining tDCS with exercise. Second, the use of sham tDCS and the implementation of robust blinding procedures allow us to control for sham effects and isolate the specific effects of tDCS.

However, one limitation of this study is that it will be conducted at a single research centre, which may restrict the generalisability of the findings. In addition, adverse events related to tDCS will be collected using standard monitoring procedures rather than a dedicated, standardised questionnaire, which may lead to under-reporting of mild or transient adverse effects.^54^

Despite these limitations, the present trial offers a unique opportunity to evaluate the efficacy of this therapeutic combination using a rigorous and controlled protocol. tDCS is a non-invasive neuromodulation technique that is already widely used in the management of other conditions, such as depression^55^ and has shown potential for implementation in home-based programmes with remote supervision.^56^ If the intervention proves to be effective, it could be translated into clinical practice to improve pain and functional outcomes in individuals with CLBP, thereby helping to reduce the associated social and economic burden.

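### The only test named for the flexion–relaxation outcome is a within-subject pre/post comparison, so a significant result could not be attributed to tDCS over sham

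*Protocol article*

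**What the plan says.** In the protocol article, the statistical section on the neuromuscular outcome (FRP) defines FRR as peak EMG activity in flexion divided by peak activity in relaxation. It then fixes the test: "Preintervention and postintervention FRR values will be compared using a paired t-test to assess statistical significance". The alternative is of the same kind: "If the assumption of normality is not met, the non-parametric Wilcoxon signed-rank test will be applied instead". No group term appears, and nothing says whether the two arms are pooled or tested separately.

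The outcome section gives the timing: "It will be assessed at baseline and post-intervention (week 4) to evaluate potential restoration". Under Objectives and hypothesis, FRP is one of three domains introduced by this sentence: "The secondary objectives are to assess the effects of repeated sessions of tDCS over the DLPFC combined with an exercise programme on". The FRP part of the hypothesis reads: "for the neuromuscular function, a restoration of FRP in the erector spinae muscles". The Statistical analysis section sets a two-sided superiority approach at the 5% level for the trial, and Secondary analysis classes the secondary outcomes as exploratory.

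**The concern.** The trial randomises between active and sham tDCS, and both arms get the same nine-session exercise programme. A pre/post change in FRR can come from exercise, the passage of time, familiarity with the bending task or regression to the mean. All of these act in both arms. A paired test asks whether FRR changed. It does not ask whether FRR changed more with active stimulation.

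Both ways of running it are unsatisfactory. Pooled over arms, it tests a shared change and carries no information about tDCS. Run per arm, it invites a reader to take significance in the active arm and non-significance in the sham arm as evidence of a difference, although the difference itself was never tested. At stake is the interpretation of one mechanistic outcome: the report could credit tDCS with restoring FRP when the data show only that FRP changed during an exercise programme.

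**Working it through.** **1. Is there a between-arm FRP test elsewhere in the article?**

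| Section | Outcome covered | Comparison named |
|---|---|---|
| Primary analysis | COMI change to week 4 | Between groups (independent-samples t-test or Mann-Whitney) |
| Clinical outcomes | COMI, ODI, VAS, HADS, FABQ, PCS | Between groups (mixed model, time-by-group term) |
| Neurophysiological outcome | EEG parameters | Between groups (unpaired, stimulation vs sham) |
| Neuromuscular outcome (FRP) | FRR | Within subject only (paired t-test or signed-rank) |

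FRR is in neither the mixed-model list nor the EEG test. The planned correlation of neurophysiological change with clinical improvement is not a between-group comparison either. FRP is the only outcome with a named test that does not compare arms.

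**2. The plan's own figure.** The article gives no figure for FRR. Its sample size is for COMI: difference 2.6, SD 3, two-sided α 0.05, power 80%. The standardised difference is 2.6/3 = 0.867. The two-sample t-test needs 21.90 per group, so 22, with power 80.2%. The stated 22 is reproduced. Dividing by 0.90 gives 22/0.90 = 24.4, which rounds up to 25 against the stated 24. That does not matter here. I use 22 completers per arm below.

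**3. How often would the paired test be significant with no tDCS effect?** Assumptions, not taken from the documents: both arms have the same mean FRR change, changes are normal, and the shift d is in units of the SD of change.

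For n pairs, the rejection rate is P(|T| > t₀.₉₇₅,ₙ₋₁), where T is noncentral t with n−1 degrees of freedom and noncentrality d√n.

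- Pooled, n = 44: d = 0.3 gives 0.3 × √44 = 1.99 and a rejection rate of 49.4%. d = 0.5 gives 0.5 × √44 = 3.32 and 90.0%.
- Per arm, n = 22: d = 0.3 gives 0.3 × √22 = 1.41 and p = 26.9%. d = 0.5 gives 0.5 × √22 = 2.35 and p = 60.9%.
- Active significant and sham not, with independent arms: p(1−p). At d = 0.3 this is 0.269 × 0.731 = 19.7%. At d = 0.5 it is 0.609 × 0.391 = 23.8%.

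| Common shift d | Pooled paired, n = 44 | One arm, n = 22 | Active significant, sham not | Between-group t-test of change (simulated) |
|---|---|---|---|---|
| 0 | 5.0% | 5.0% | 4.8% | 4.9% |
| 0.2 | 25.4% | 14.6% | 12.5% | not run |
| 0.3 | 49.4% | 26.9% | 19.7% | 4.8% |
| 0.5 | 90.0% | 60.9% | 23.8% | 4.8% |
| 0.8 | 99.9% | 94.7% | 5.0% | 5.1% |

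The last column is from 40,000 simulated trials per row. The same simulation agreed with the pooled and per-arm formulas (for example 89.8% and 23.7% at d = 0.5). The pooled and per-arm columns are alternative readings of the article and cannot both apply.

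**The case against.** Four points can be made for the plan.

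*The hypothesis speaks of restoration.* The comparison with sham is spelled out for the clinical outcomes. The FRP clause is separate and names no comparator, so a pre/post test matches its literal wording. This stands as a reading of that clause. It does not rescue the test, because the same section lists FRP among the effects of tDCS with exercise, and the superiority approach is stated for all primary and secondary outcomes.

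*The outcome is exploratory.* Main conclusions come from COMI. This stands, and it limits the severity. It excuses low power or light multiplicity control, but not a prespecified test that leaves the randomised comparison unused.

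*The gap could be filled.* Both arms are measured at both visits, and a separate analysis plan may add a comparison. The data will indeed allow one. But the article does not leave the test open: it names one of the wrong kind, so this is not a detail deferred to another document.

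*The Discussion's claim is general.* The statement that sham and blinding "allow us to control for sham effects and isolate the specific effects of tDCS" describes the design. Of FRP the Discussion says only that, with EEG, it may help explain mechanisms. A reader might infer that the authors promise an FRP effect over sham, or that they have decided to discard the sham control for FRP. The text supports neither. It shows only that the one named FRP test does not use that control.

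A reader might also infer that FRR must be strongly skewed because its denominator is small when the muscle relaxes. The documents give no FRR distribution. They say FRP is reduced or abolished in about half of people with low back pain, so many denominators need not be near zero, and a rank-based fallback is provided. The point does not depend on skewness.

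**Conclusion.** The concern holds. As written, the FRP analysis cannot attribute a change in FRR to tDCS over sham, whether pooled or run per arm. This follows from the form of the test and needs no numerical assumption.

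The size is illustrative. It assumes no tDCS effect, 22 completers per arm, normal changes and a common shift of 0.3 to 0.5 SD, for which the documents offer no source. Under those assumptions the pooled test is significant in about 49% to 90% of trials, and the misleading per-arm pattern occurs in about 20% to 24%. One might be tempted to quote the chance that exactly one arm is significant (39% to 48%), but half of that is the opposite pattern, with only sham significant. With no common shift the misleading pattern falls below 5%.

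Severity: should be fixed. The primary COMI analysis, the sample size and the main conclusion are untouched.

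**What to change.** Replace the paired test with a between-arm comparison of week-4 FRR adjusted for baseline FRR (ANCOVA), reported as an estimate with a 95% CI. Use the log scale if the ratio proves skewed; an unpaired or rank-based test of change would also repair the defect. Replace the signed-rank fallback too, since it has the same fault. Give within-arm changes descriptively, without p-values.

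The cost is about two sentences of analysis text, plus the ethics and registry update that the article promises for amendments. No measurements are added. The change should be made while the statisticians are still blinded, because a comparison added after results are seen would be post hoc.

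The repaired analysis will not be well powered. With 22 per arm, a between-group t-test of change has about 16%, 37% and 74% power for true differences of 0.3, 0.5 and 0.8 SD. The confidence interval should therefore carry the interpretation, and a non-significant result should not be read as no effect.
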